#### Sample Size Calculation

The sample size has been estimated based on power analysis using G*Power 3.1. [72]. The following parameters were set on the sample size calculator: effect size of f = 0.21, mixed analysis of variance (ANOVA) including within-subject (3-time points), and between-subject (2 groups); effects were with 95% power and at a two-sided 5% significance level. Results suggested that the minimum required sample size was 60 participants. However, considering the percentage of drop-out occurring in Internet-based intervention for university students [73], a drop-out rate of around 25% was expected. For this reason, it is planned to recruit approximately 90 participants.

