## 3. Statistical Analysis

SPSS (IBM) version 27 will be used to process data. Descriptive analyses will be run on sociodemographic variables, data related to the satisfaction questionnaires, and SCL-90-R and WHODAS 2.0 scores. Chi-Square tests and Student’s *t*-tests will be run to investigate differences between participants in the two conditions on baseline demographic variables, gender variables, age, and all baseline measures. If some variables significantly differ between conditions, they will be considered as covariants in the following analyses. A series of mixed models of analysis of variance (ANOVAs) will be run to investigate the efficacy of the intervention on the SIB-S, PGWBI, RRS, ARQ, PSWQ, TAS-20, and SII scores, as a function of the factor between CONDITION (ComunicaBene vs. Waitlist) and the factor within TIME (Baseline vs. Post-Intervention vs. Follow-Up). The level of significance will be set at *p* < 0.05. Effect sizes will be calculated using partial eta squared and interpreted based on benchmarks that Cohen (2013) suggested: η_p_^2^ = 0.01, small effect size; η_p_^2^ = 0.06, medium effect size; η_p_^2^ = 0.14 large effect size. The post hoc analyses of significant interaction will be conducted using the LSD post hoc test.

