The main difference corresponding to the innovative strategies proposed with ComunicaBene is the substitution of the in vivo-practice with imagery practice. Practice is an essential component of every assertive training, and, as previously mentioned, it can be insufficient or absent in online assertive training. The use of imagination could fill this gap, as mental imagery allows one to create, reactivate, and manipulate internal representations without a direct external stimulus [62]. We hypothesized that by mentally rehearsing specific behaviors and scenarios, participants would enhance their communication skills and improve their overall social performance [51]. Specifically, we believe that allowing individuals to create a positive mental image of the future and visualizing themselves performing at their best will increase their confidence and self-efficacy [56,97,98,99]. Moreover, by mentally rehearsing specific interpersonal scenarios, individuals can prepare themselves mentally for potential challenges, reducing uncertainty and distress [90,100]. Overall, we hypothesized that behavior rehearsal and in vivo-role playing could be replaced with imagery techniques, making assertiveness practice possible via the Internet. 

ComunicaBene will also include an in vivo-exposure, as participants in the last phase will have to act out what they have previously learned in real-life situations. The aim is to improve and generalize their learning by practicing their ability and evaluating their change and the consequences of assertive behavior [3]. Therefore, we hypothesize that even after the end of the training, participants will be able to act assertively even in entreated situations [47] and that thanks to repeated practice, the improvements could be maintained over time [1].

Moreover, as previously mentioned, ComunicaBene includes regular monitoring of a Tutor. Therefore, we expect adherence to the intervention, as the Tutor helps participants to maintain motivation in carrying out the program [101]. Moreover, we believe that the Tutors may foster the effectiveness of the intervention and promote change in the participants, as they will serve as a model of assertive behavior [95], a reinforcement of students’ effort and success [96], and will help participants to identify cognitive biases, irrational thoughts, and catastrophic scenarios, and replace them with alternative and more realistic ones [94]. 

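### The interaction partial eta squared does not quantify whether the benefit lasts to six months, and its size label depends on an unstated correlation between visits

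*Protocol article*

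**What the plan says.** Section 3, Statistical Analysis, plans mixed ANOVAs for every outcome, with CONDITION as the between factor and TIME (baseline, post-intervention, follow-up) as the within factor. On software it says "SPSS (IBM) version 27 will be used to process data". On magnitude it says "Effect sizes will be calculated using partial eta squared and interpreted based on benchmarks" of 0.01 (small), 0.06 (medium) and 0.14 (large). It names no other effect measure and no confidence interval. A significant interaction is to be followed by LSD post hoc tests; the contrasts are not listed.

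The Sample Size Calculation uses "effect size of f = 0.21, mixed analysis of variance (ANOVA) including within-subject (3-time points), and between-subject (2 groups", adds that "effects were with 95% power and at a two-sided 5% significance level", and reports that "the minimum required sample size was 60 participants". It does not state the correlation between visits.

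The Discussion hypothesises that "the improvements could be maintained over time", and section 2.1 schedules a follow-up six months after the intervention.

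**The concern.** An efficacy trial with a six-month follow-up has to answer two questions about size: how large the between-arm difference is when the programme ends, and how much of it remains six months later. The interaction partial eta squared condenses the departures from parallel profiles over all three visits into one number without sign or unit. Two quite different courses can give the same number. Its denominator is within-subject error, so the number also depends on how strongly scores correlate between visits. One set of cut-offs is to be applied to seven instruments whose correlations need not agree, so equal benefits could receive different labels.

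At stake is how the efficacy result is described. The validity of the significance test is not at stake.

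**Working it through.** **Inputs.** From the Sample Size Calculation: f = 0.21, 2 groups, 3 time points, 95% power, two-sided 5% level, N = 60. From section 3: the 2 × 3 mixed ANOVA, SPSS, and the benchmarks 0.01, 0.06 and 0.14. Assumed, because the article does not give them: 1:1 allocation, SD equal across visits, a common correlation r between visits, and partial eta squared taken from the univariate interaction test.

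**1. The plan's own figure.** The noncentrality for the interaction is f²·N·m/(1 − r), with m = 3 visits. At r = 0.5 this is 0.21² × 60 × 3 / 0.5 = 15.88, with df 2 and 2 × (60 − 2) = 116. Power is 0.950, so N = 60 is reproduced. Other correlations on the same scale give 84 (r = 0.3), 72 (0.4), 50 (0.6) and 38 (0.7), so the stated minimum implies r of about 0.5.

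**2. Lasting versus vanished benefit.** Let δ be the between-arm difference at each visit, in SD units. The population partial eta squared for the interaction is S / (S + 2(1 − r)), where S is the sum of squared deviations of the three δ from their mean, divided by 4.

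- Lasting, (0, d, d): mean 2d/3; sum of squares 4d²/9 + d²/9 + d²/9 = 2d²/3; S = d²/6.
- Vanished, (0, d, 0): mean d/3; sum of squares d²/9 + 4d²/9 + d²/9 = 2d²/3; S = d²/6.

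The two agree for every d and r. An effect present only at six months, (0, 0, d), gives the same value again. For d = 0.8 and r = 0.5: S = 0.64/6 = 0.1067, and 0.1067/(0.1067 + 1) = 0.096 for each.

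Simulation with 30 per arm, d = 0.8 and 4,000 runs gave mean values of 0.110 (lasting) and 0.112 (vanished) under a common correlation of 0.5. Under serial correlation of 0.7 they were 0.141 and 0.144. In the common-correlation runs, a two-sample comparison at six months was significant in about 85% of lasting cases and about 5% of vanished ones. The data separate the two courses; this summary does not.

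**3. Dependence of the label on r.** For d = 0.5, S = 0.25/6 = 0.0417:

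| r | 0.3 | 0.5 | 0.7 | 0.8 | 0.9 |
|---|---|---|---|---|---|
| partial eta squared | 0.029 | 0.040 | 0.065 | 0.094 | 0.172 |
| label | small | small | medium | medium | large |

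For comparison, in a two-group contrast at one visit f = d/2 and eta squared is f²/(1 + f²). Differences of 0.2, 0.5 and 0.8 SD then give 0.010, 0.059 and 0.138, which match the stated benchmarks to two decimals. The interaction value puts these three differences in the small, medium and large bands when r is about 0.67 to 0.87. Below that range they fall one band lower. Above it the 0.5 SD difference is labelled large.

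**4. The planning effect.** For (0, d, d), f² = d²/18, so f = 0.21 means d = 0.21 × √18 = 0.89 SD. Its population value in SPSS at r = 0.5 is 15.88/(15.88 + 120) = 0.117, labelled medium.

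**The case against.** Four objections have force.

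- **The plan is not blind to timing.** A reader might infer that the trial cannot tell a lasting effect from a vanished one. That goes too far. After a significant interaction, the LSD tests can compare the arms at six months. Section 3 also does not restrict partial eta squared to the interaction, and the CONDITION main-effect value does differ: 0.096 (lasting) against 0.026 (vanished) at d = 0.8 and r = 0.5. What remains is that the LSD tests are conditional, have no stated contrasts and carry no effect size or interval, while the main effect is averaged with baseline and does not isolate the six-month difference.
- **The labels are not always off.** A reader might infer that SPSS inflates the effect, because converting f = 0.21 directly gives 0.21²/(1 + 0.21²) = 0.042 (small) against 0.117 (medium). The two figures are on different scales. The underlying difference of 0.89 SD exceeds 0.8, so medium, if anything, understates it. For r of about 0.67 to 0.87 the labels are as expected.
- **Noise and sample size.** With no effect and N = 60, partial eta squared reaches 0.01 in 0.99^58 = 56% of trials. But values below about 0.050 are non-significant under the p < 0.05 rule and trigger no post hoc tests, so this is no separate fault. Nor does the article say where f = 0.21 came from. Any claim that it was taken from another scale and that 60 is therefore too few is conjecture, and 60 reproduces as stated.
- **An article condenses.** Per-visit differences and intervals may stand in a fuller plan, and naming partial eta squared does not exclude them. This is fair, and it limits the weight of the point. The point rests on the measure and labels that the article does fix.

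**Conclusion.** The point holds as one about effect-size reporting. As the article stands, its only named effect measure, read from the interaction, is identical for a lasting and a vanished benefit (0.096 for both at d = 0.8, r = 0.5), so it does not quantify the hypothesised maintenance. Its label for a fixed 0.5 SD difference runs from small at r = 0.5 to medium at r = 0.7, and the article gives no r. At the r = 0.5 that reproduces N = 60, the planning effect of about 0.89 SD would be labelled medium.

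These figures assume 1:1 allocation, equal SDs, a common correlation and the univariate interaction test. The F test, its error rate and the sample size stand. This is an inexpensive improvement that should be made; it does not threaten the trial's inference.

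**What to change.** For s-SIB distress and s-SIB performance, state that the baseline-adjusted between-arm mean difference with 95% CI will be reported at post-intervention and separately at six months. Give it in scale points and divided by the pooled baseline SD, whether or not the interaction is significant. Keep partial eta squared as a supplementary figure, and do not base the efficacy conclusion on its benchmark labels.

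The adjusted difference is not a direct output of the planned mixed ANOVA, so the cost is a small additional model per visit for each scale, one output table and a change of wording. No new data are needed, and the sample size and significance test stay as they are.

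### Efficacy rests on an undirected three-level interaction followed by an open set of unadjusted LSD comparisons, which gives only weak error control and names no between-arm contrast at post-intervention or 6 months

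*Protocol article*

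**What the plan says.** Section 3 (Statistical Analysis) plans one mixed ANOVA per questionnaire, with condition as the between-subject factor and "the factor within TIME (Baseline vs. Post-Intervention vs. Follow-Up") as the within-subject factor, at p < 0.05. On size of effect it says "Effect sizes will be calculated using partial eta squared", read against small, medium and large benchmarks. On what follows a significant interaction it says "The post hoc analyses of significant interaction will be conducted using the LSD post hoc test".

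The Sample Size Calculation uses the same design: "effect size of f = 0.21, mixed analysis of variance (ANOVA) including within-subject (3-time points), and between-subject (2 groups"), and "effects were with 95% power and at a two-sided 5% significance level". The result is given as "Results suggested that the minimum required sample size was 60 participants".

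Section 2.1 sets assessments at baseline, post-intervention and 6 months. Section 2.4.2 keeps the waitlist arm untreated until after the follow-up assessment, so a randomised comparison is available at both post-baseline visits. Section 3 names neither as the efficacy test.

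**The concern.** The trial asks two questions: does the programme raise assertiveness by its end (section 1.2), and does the gain last (section 4). Each is answered by a difference between randomised arms at a visit. The 2-df interaction answers neither alone. It says only that the arm difference is not constant over the three visits. It is significant for a benefit at post-intervention, a benefit at 6 months, or harm at either. Partial eta squared inherits this: it carries no sign and no scale unit.

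The conclusion therefore falls to the LSD step. LSD makes no adjustment for the number of comparisons, and the text does not limit them. A 2 x 3 table offers three between-arm comparisons (one per visit) and three between-visit comparisons within each arm, nine in all. Six are within-arm changes, which randomisation does not support as evidence of a treatment effect. At stake is whether the reported efficacy result is a pre-set randomised contrast or a selection from nine unadjusted tests.

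**Working it through.** **Inputs.** From the document: f = 0.21, two groups, three time points, alpha 0.05, power 95%, minimum N = 60, expected drop-out about 25%, recruitment about 90. Not in the document and assumed here: 1:1 allocation, correlation r = 0.5 between visits, sphericity, normal data.

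**1. The plan's own figure.** For the group-by-time interaction, lambda = f² x N x m / (1 - r) = 0.0441 x 60 x 3 / 0.5 = 15.88, with df = 2 and 2 x (60 - 2) = 116. Power is 95.0%, and 60 is the smallest N that reaches 95%. At r = 0.3, 0.4, 0.6 and 0.7 the N would be 84, 72, 50 and 38. The between-subject main effect would need 200. So 60 fits the interaction test (or the TIME effect, which has the same lambda and df), not an arm difference at a named visit. Drop-out does not alter this point: 60 / 0.75 = 80, below 90.

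**2. Effect implied by f = 0.21.** If the arms differ by d SD at both post-baseline visits, f = d / sqrt(18), so d = 0.21 x 4.243 = 0.89. The same d results if the difference is at one visit only.

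**3. Error rates of the gate followed by LSD, one scale.** Simulated trials (40,000 per scenario), 30 per arm: interaction F-test at 0.05, then unadjusted pairwise tests at 0.05.

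| Truth | Family of LSD tests | False-positive rate |
|---|---|---|
| No effect at any visit | All nine | just under 5% |
| No effect at any visit | Post and 6-month between-arm | 1.6% |
| Effect at one visit only | Post and 6-month between-arm | about 5% |
| 0.89 SD at post only | The six true nulls among the nine, in trials passing the gate | about 22% |

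In the last row the gate is passed in 95% of trials, so it filters out almost nothing. The six true nulls are the between-arm differences at baseline and 6 months, the baseline-to-6-month change in the ComunicaBene arm, and the three waitlist changes. The components are a false waitlist change in about 12% and a false 6-month between-arm difference in about 5%. At 45 per arm the total is again 22%.

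**4. Direction.** With a harmful 0.89 SD difference at 6 months only, the interaction is significant in about 95% of trials, the same rate as for a benefit of that size at post only.

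**5. Power for 0.5 SD at both visits, 30 per arm.**
- Omnibus interaction: f = 0.5 / sqrt(18) = 0.118, lambda = 0.01389 x 60 x 3 / 0.5 = 5.0, power 49%.
- Post contrast without baseline adjustment: 0.5 / sqrt(2/30) = 1.94, power 48%. The change score gives the same at r = 0.5, because its variance is 2(1 - r) = 1.
- Post contrast adjusted for baseline: residual variance 1 - r² = 0.75, so 0.5 / sqrt(0.75 x 2/30) = 2.24, power 59%.

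**The case against.** The strongest reply is that the plan does control error where it matters. LSD runs only after a significant interaction. With no treatment effect, this caps any false post hoc claim at about 5% however many comparisons follow. For the two between-arm contrasts that bear on efficacy, the rate also stays at about 5% when one of them is a true effect, since only one null is then left. This stands. A reader might infer from the word LSD that the post hoc claims have no error control at all; the figures above do not support that.

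It is also fair that the article never says all nine comparisons will be tested, and never proposes to infer efficacy from a change in one arm and none in the other. The interaction is itself a randomised comparison of change. The 22% therefore describes what the open wording permits, not what the authors have announced. But the wording does not exclude it: LSD on a significant interaction, with no contrasts listed, covers within-arm and between-arm pairs alike.

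A third reply is that contrasts are often left to an analysis plan, which is not shown. That would hold if the article were silent. It is not: it fixes the post hoc method and the effect measure, and the point is how that stated rule performs.

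A reader might also infer that the omnibus test wastes power. The figures do not show this: 49% for the omnibus test against 48% for an unadjusted post contrast. The rise to 59% comes from adjusting for baseline.

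**Conclusion.** The concern holds in a limited form. The gate gives weak control only: about 5% per scale under no effect, about 5% if LSD is confined to the post and 6-month between-arm contrasts, and about 22% of gate-passing trials with at least one false result if all nine comparisons are open and the effect is at post only. Neither the interaction nor its partial eta squared states the direction or the time of a difference, and no decisive between-arm contrast is named.

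The 22% rests on 1:1 allocation, r = 0.5, sphericity, normal data and a 0.89 SD effect; it hardly changes between 30 and 45 per arm. It does not mean that 22% of trials would make a false efficacy claim, since four of the six nulls are the baseline between-arm comparison and the waitlist's own changes. The matter should be settled before analysis; it does not undermine the design.

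**What to change.** In section 3, replace the LSD step by two named between-arm contrasts, at post-intervention and at 6 months, each adjusted for the baseline score and reported with a 95% CI. The present ANOVA cannot supply these, because it treats baseline as a level of TIME and its contrasts are differences in change scores. Use ANCOVA at each visit, or a longitudinal model with baseline as a covariate or constrained equal between arms.

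Either name the decisive visit in advance or apply a simple multiplicity rule to the two contrasts. Testing post first and 6 months only if post is significant is one option. It would, however, block a claim of delayed effect, and the limitations in section 4 allow that change may need more real-life practice. Splitting alpha avoids this at small cost: with 30 per arm and 0.89 SD, the baseline-adjusted power per contrast is 97.5% at 0.05 and 95.1% at 0.025.

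Report within-arm changes as means with no tests. The cost is a small change of model and a few sentences, plus either a conditional or a slightly stricter second test. No extra data or visits are needed.

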## 4. Discussion

The importance of communication skills for mental health and self-realization is widely accepted [4,5,6,7]. However, despite its clear usefulness, research on assertiveness and assertive training has declined significantly in the past decades [10]. Consequently, traditional training does not consider the most recent novel technologies used to spread psychological interventions. This is not in line with the more recent evidence suggesting the importance of using innovative strategies to deliver mental health interventions, such as the Internet, to reach more people, reduce costs, and overcome structural barriers [24]. Overall, while promoting assertiveness through the Internet offers many benefits, some potential obstacles and criticisms need to be considered. For example, online assertive training may not provide the same level of personal interaction as in-person training, and it can compromise the needed practice required in assertive training. Moreover, online training may not provide the same feedback and support as in-person training. This can make it more difficult for individuals to assess their progress and improve their assertiveness skills. 

ComunicaBene, a guided Internet-based imagery intervention to promote assertiveness, has been developed to address these challenges. This paper presents the study protocol for a randomized controlled trial that will be conducted to investigate the efficacy and the acceptability of the intervention. 

ComunicaBene includes some of the phases of traditional assertive training: the initial assessment, which aims to evaluate the level of assertiveness and to identify the most difficult interpersonal situations; the commitment and motivation phase, which aims to help participants consider the costs and benefits of changing and to set personal goals; and the psychoeducational phase, which aims to help participants to recognize and distinguish different communication styles, to learn the main principles of assertive communication, and to improve their awareness and to accept their rights and others’ rights. We hypothesize that working on these elements will help participants become more aware of their needs, emotions, communication style, and interpersonal functioning [3].

The main difference corresponding to the innovative strategies proposed with ComunicaBene is the substitution of the in vivo-practice with imagery practice. Practice is an essential component of every assertive training, and, as previously mentioned, it can be insufficient or absent in online assertive training. The use of imagination could fill this gap, as mental imagery allows one to create, reactivate, and manipulate internal representations without a direct external stimulus [62]. We hypothesized that by mentally rehearsing specific behaviors and scenarios, participants would enhance their communication skills and improve their overall social performance [51]. Specifically, we believe that allowing individuals to create a positive mental image of the future and visualizing themselves performing at their best will increase their confidence and self-efficacy [56,97,98,99]. Moreover, by mentally rehearsing specific interpersonal scenarios, individuals can prepare themselves mentally for potential challenges, reducing uncertainty and distress [90,100]. Overall, we hypothesized that behavior rehearsal and in vivo-role playing could be replaced with imagery techniques, making assertiveness practice possible via the Internet. 

ComunicaBene will also include an in vivo-exposure, as participants in the last phase will have to act out what they have previously learned in real-life situations. The aim is to improve and generalize their learning by practicing their ability and evaluating their change and the consequences of assertive behavior [3]. Therefore, we hypothesize that even after the end of the training, participants will be able to act assertively even in entreated situations [47] and that thanks to repeated practice, the improvements could be maintained over time [1].

Moreover, as previously mentioned, ComunicaBene includes regular monitoring of a Tutor. Therefore, we expect adherence to the intervention, as the Tutor helps participants to maintain motivation in carrying out the program [101]. Moreover, we believe that the Tutors may foster the effectiveness of the intervention and promote change in the participants, as they will serve as a model of assertive behavior [95], a reinforcement of students’ effort and success [96], and will help participants to identify cognitive biases, irrational thoughts, and catastrophic scenarios, and replace them with alternative and more realistic ones [94]. 

Regarding the acceptability of the intervention, we expect that participants will be satisfied with the program, as young people usually report high satisfaction and perceived utility with online programs [23]. 

Besides these expectations, it is also important to consider some possible limitations and obstacles: ComunicaBene is a quite brief intervention, and changes may occur after more in vivo exposure [102]. Moreover, the situation proposed in the audio tracks may not fit the needs of every participant. Participants’ difficulty immersing themselves in the imagined interactions proposed could compromise the effectiveness of the imaginative sessions. If this study will point out this limitation, we will develop more audio tracks, allowing students to choose the one that better suits their needs and experiences. 

In conclusion, we expect some noteworthy results from this study. First of all, the study’s findings will shed light on the potential effect of ComunicaBene on assertiveness. Considering the role of assertiveness in contributing to mental health and well-being [4,5] and the role of unassertiveness in contributing to psychopathology [10], ComunicaBene may be both an efficacious prevention and promotion intervention. Moreover, it is a scalable and affordable intervention and could overcome all the limitations related to traditional services, such as high costs, lack of services in specific areas, and long waiting lists [24]. ComunicaBene has been designed for university students; however, the program can easily be adapted to other target audiences (e.g., workers, parents, and teachers) by developing new audio tracks based on their specific needs and characteristics. Therefore, the applicability of ComunicaBene could even be expanded. Moreover, this study will propose a new insight into integrating imagery techniques within assertiveness training. Lastly, the findings of this study will provide new evidence about the use of the Internet to spread communication skills training. It will provide a series of advantages: individuals can easily access anytime and anywhere to reliable resources, have the opportunity to practice assertiveness with a Tutor at a reduced cost, compared to in-person training, and the Tutor can constantly monitor the participants’ progress, providing them feedback and reinforcement; moreover, to conclude, interventions spread through the Internet can reach a great number of people.

